#### Data analysis

Analyses will be by intention to treat, including withdrawals and losses to follow-up. Study groups will be compared in terms of baseline characteristics. As this is a randomised trial, we would anticipate minimal differences in baseline characteristics. If however, important differences are found, these potential confounders will be adjusted for in the analysis of outcomes. For the primary outcomes, the mean score for each measure for each group will be compared using t-tests. If adjustment for confounders is needed a multiple linear regression model will be used. The secondary outcomes will be compared using chi-square tests of significance for categorical data and t-tests for continuous data. If adjustment for confounding is necessary logistic regression and multiple linear regression will be used respectively.

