### Outcome measures

#### Baseline data collection

Brief baseline data will be collected to assess comparability of the study groups. The baseline assessment will include age, parity, brief socio-demographic data, highest level of education achieved, knowledge and anxiety as assessed by the state component of the short Spielberger anxiety scale[42].

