#### Primary outcomes

The effectiveness of risk communication to aid patient decision making is best assessed by a combination of cognitive, affective and behavioural outcomes[43]. Thus the primary outcomes of the this study will be

• cognitive: change in knowledge and realistic expectations of the management options and possible benefits and risks of each option

• affective: anxiety, satisfaction with the decision, participation in decision-making and the amount of decisional conflict (uncertainty about which course of action to choose) experienced

• behavioural: actual decision taken and acted upon (see secondary outcomes)

Measures of knowledge and realistic expectations about options for the management of breech presentation and the benefits and risks of ECV will be specific to this project. Thus we will need to develop, and test these measures as part of the project.

Anxiety will be measured by the state component of the short Spielberger anxiety scale which has been extensively used and validated[42]. We do not anticipate the decision aid will increase women's anxiety but it is nevertheless important to document any increase or decrease in anxiety attributable to the decision aid.

Satisfaction with the decision will be assessed using the Satisfaction with Decision Scale. Satisfaction with Decision Scale (a very brief six item scale with high reliability) was developed specifically to assess satisfaction with health care decisions[44].

Participation in decision-making will be ascertained using the five-item Degner Control Preferences Scale[45]. This allows respondents to specify the degree of control in decision-making they wish to assume with their doctor.

Decisional conflict will be assessed by the Decisional Conflict Scale which has established reliability, good psychometric properties and is short (16 items)[46]. It has been used to evaluate a range of decision aids[35].

Because the decision about ECV must be made within a short timeframe, the outcomes will be measured as soon as practical after the consultation in which the ECV decision was made – prior to the next antenatal visit. For the primary outcomes this will be within one week of the decision being made (Figure 1, 1^st ^follow-up).

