### Statistical issues

#### Sample size

Sample size calculations for the trial (significance 0.05, power 0.8) were determined using the mean difference we would like to detect in women's decisional conflict scores and knowledge of options and outcomes. Compared with usual care, decisional conflict was shown in the most current systematic review to be significantly reduced by decision aids; the meta-analysed mean difference was -5.75, 95%CI -8.63, -2.87 (on a scale ranging from 1 lowest to 5 highest decisional conflict; median standard deviation 13.25)[48]. Assuming a mean difference of -5.75 and standard deviation 13.25, we would need approximately 84 women in each arm to demonstrate changes in decisional conflict. The meta-analysis also showed that for nine trials comparing decision aids and usual care, decision aids improved average knowledge scores by 18.75 points (out of 100) (95%CI 13.1 to 24.4, median standard deviation 20)[48]. To show such a difference, assuming mean difference of 18.75 and standard deviation of 20, would require only 18 women in each arm. Because we would like to be able to show differences in decisional conflict if they exist, we have used the larger sample size estimate. Although follow-up will be relatively short term, there will inevitably be some loss to follow-up. To allow for 10% loss to follow-up the sample size calculated above (84) is inflated by 10% to give the effective sample size of 92 women per arm and a total sample of 184 for the trial. This sample size is different from our original application for funding. Originally, we estimated a sample size of 310 women (155 in each arm). This was based on results from a 1999 systematic review of only 2 trials of decision aids versus usual care that had assessed decisional conflict[35]. Subsequent to the submission (January 2001) and funding of this protocol (March 2002) the systematic review was updated (2002) incorporating 6 trials that assessed decisional conflict[48]. At that time we revised the sample size estimate to incorporate the most current research evidence available. Ethics approval was obtained for the protocol amendment.

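### Adjusting the primary comparisons only when baseline differences look important gives up precision that the baseline scores already collected would supply, chiefly for anxiety

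*Protocol article*

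**What the plan says.** Under Data analysis, the primary outcomes are handled so that "the mean score for each measure for each group will be compared using t-tests". The section expects randomisation to leave little imbalance, then adds a contingency: "If however, important differences are found, these potential confounders will be adjusted for in the analysis of outcomes". The model in that case is multiple linear regression.

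Under Baseline data collection, the variables include age, parity, socio-demographic items and "highest level of education achieved, knowledge and anxiety as assessed by the state component" of the short Spielberger scale. Their stated purpose is to check that the groups are comparable. Decisional conflict and satisfaction are not in the baseline list.

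Under Primary outcomes, the cognitive outcome is introduced as "cognitive: change in knowledge and realistic expectations of the management options", whereas Data analysis speaks of mean scores.

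**The concern.** Randomisation makes any baseline imbalance a chance event, so its observed size is a poor reason to adjust. The good reason is prognostic strength, and a woman's own earlier score on the same scale is an obvious candidate that can be named in advance. The stated rule works the other way. When the groups look balanced, which the protocol expects, the baseline scores are not used. When they do not, the estimator changes after the data have been seen.

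At stake are the precision of the knowledge and anxiety comparisons and a primary estimate fixed beforehand. Anxiety matters most. It is a primary outcome with no effect size in the Sample size section, and Ethical considerations relies on its baseline and follow-up measurements to document adverse effects.

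**Working it through.** **Inputs from the protocol (Sample size).** The basis is "Sample size calculations for the trial (significance 0.05, power 0.8"); two-sided testing is inferred because it reproduces the stated numbers. For decisional conflict: "Assuming a mean difference of -5.75 and standard deviation 13.25, we would need approximately 84 women in each arm". For knowledge: "assuming mean difference of 18.75 and standard deviation of 20, would require only 18 women in each arm". The 84 "is inflated by 10% to give the effective sample size of 92 women per arm and a total sample of 184".

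**Inputs assumed.** The protocol gives no correlation r between baseline and follow-up, so r = 0.3, 0.5 and 0.7 are shown. The 0.3 SD effect is illustrative. The protocol sets no numerical trigger for adjustment, so baseline p<0.05 stands in for it.

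**1. Reproduce the plan's figures.** n per arm = 2 × (SD/difference)² × (1.960 + 0.842)².
- Decisional conflict: 2 × (13.25/5.75)² × 7.85 = 83.4, rounded up to 84.
- Knowledge: 2 × (20/18.75)² × 7.85 = 17.9, rounded up to 18.

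Both agree with the protocol. They use the unadjusted formula, so the sample size takes no credit for baseline covariates. With 92 recruited per arm and 10% lost, 92 × 0.9 = 82.8, or about 83 analysed.

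**2. Residual variance.** ANCOVA leaves (1 − r²) of the unadjusted variance. A t-test on change scores leaves 2(1 − r).

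| r | ANCOVA variance | Reduction | Equivalent extra women, 1/(1 − r²) − 1 | Change-score variance |
|---|---|---|---|---|
| 0.3 | 0.91 | 9% | 10% | 1.40 |
| 0.5 | 0.75 | 25% | 33% | 1.00 |
| 0.7 | 0.51 | 49% | 96% | 0.60 |

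The change score is less efficient than ANCOVA at all three values, and no better than the plain t-test at 0.3 and 0.5.

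**3. Power and type I error, 83 per arm.** Trials were simulated with a 0.3 SD effect for power and no effect for type I error.

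| r | Power, conditional rule | Power, ANCOVA | Type I error, conditional rule |
|---|---|---|---|
| 0.3 | 49% | 52% | 4.9% |
| 0.5 | 48% | 59% | 4.5% |
| 0.7 | 50% | 77% | 3.7% |

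The ANCOVA column can be checked by the normal approximation Φ(0.3 × √(83/2)/√(1 − r²) − 1.96). Since 0.3 × √41.5 = 1.933, dividing by 0.954, 0.866 and 0.714 gives 2.03, 2.23 and 2.71, hence 53%, 61% and 77%. These agree to within simulation error and the approximation.

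**4. The same gain at 84 per arm.** The unadjusted t-test detects 2.80 × √(2/84) = 0.432 SD with 80% power. Multiplying by √(1 − r²) gives a detectable difference of 0.412 / 0.374 / 0.309 SD. Equivalently, power for 0.432 SD rises from 80% to 83.6% / 89.9% / 97.5%.

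**5. Knowledge at its own planning effect.** The unadjusted standard error is 20 × √(2/84) = 3.09 points. Then 18.75/3.09 = 6.07, and power exceeds 99.9% without adjustment. ANCOVA reduces the standard error to 2.94 / 2.67 / 2.20 points, so only the interval narrows.

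**The case against.** The case for leaving the plan alone has substance. The unadjusted t-test is valid under randomisation and matches the basis of the sample size. The gain in power rests on a correlation and an effect size that the protocol does not supply, and at r = 0.3 it is only about 3 percentage points. A low correlation is plausible for knowledge, since the intervention teaches the content being tested. The definition of an important difference and the covariate list may sit in a fuller document that is not shown, so their absence is not held against the article. All of this stands. It limits the size of the point but does not remove it, because the conditional rule is stated outright.

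Three stronger readings are tempting and not supported.
- **The rule inflates false positives.** Under the fixed trigger assumed here, the type I error is at or below 5%. Inflation would need a free choice between the adjusted and unadjusted results, which the protocol does not state.
- **Two of the four primary outcomes lose meaningful power.** Knowledge does not, on the protocol's own planning figures.
- **The knowledge outcome is defined in contradictory ways.** Change may describe a change score, or may loosely restate the hypothesis that knowledge increases. This is an ambiguity that one sentence can settle.

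**Conclusion.** The point holds as one of efficiency and pre-specification. It should be corrected, but it does not threaten the trial's validity. Under the assumed correlations of 0.3 to 0.7, always adjusting for the baseline score removes 9% to 49% of residual variance. At an illustrative 0.3 SD effect, it adds about 3, 11 and 27 percentage points of power over the conditional rule. The practical benefit falls mainly on anxiety, and its true size is unknown because the protocol states neither an effect size nor a correlation for it.

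A reader might infer that the trial is wrongly sized. The documents do not support that: 84 per arm reproduces. Decisional conflict, which sets that number, has no listed baseline measure, and neither does satisfaction. No gain from adjustment is demonstrated for either.

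**What to change.** In Data analysis:
- **Knowledge and anxiety.** Replace the imbalance-triggered rule with a linear regression of the first follow-up score on arm and the baseline value of the same score, fitted whatever the observed balance. Keep the unadjusted t-test as a supporting analysis.
- **Definition of the knowledge outcome.** State that knowledge is analysed as the baseline-adjusted follow-up score, and align the Primary outcomes wording with this.
- **Decisional conflict and satisfaction.** Drop the imbalance trigger. Adjustment for parity or other baseline covariates is optional, provided they are fixed in advance.

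The cost is a change of wording before the data are analysed. The baseline scores and parity are already collected, and the sample size stays as it is.

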### Hypotheses

The primary hypotheses of the study are:

Use of the ECV decision aid by women with a singleton breech-presenting infant in late pregnancy

1. increases knowledge about breech presentation and the management options

2. reduces decisional conflict (uncertainty about the course of action)

3. increases satisfaction with decision making

4. reduces anxiety

The secondary hypotheses of the study are:

Use of the ECV decision aid by women with a singleton breech-presenting infant in late pregnancy does not influence

1. uptake of ECV

2. the proportion of women having a planned caesarean section for breech presentation at term

3. maternal and infant outcomes

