#### Secondary outcomes

The aim of the decision aid is to assist patient decision making, and not to influence the direction of the decision taken. Nevertheless, we think it is important to collect service utilisation and pregnancy outcome data so we will record and compare the numbers of ECVs undergone and ECV success rate in both arms of the study, as well as recording and comparing rates of pregnancy complications and perinatal outcomes. Data on ECVs are already prospectively collected for quality assurance, these include fetal lie, parity, success rates and complications. Other perinatal outcomes will be obtained (with informed consent) from the existing computerised obstetric database. These outcomes include mode of delivery (vaginal, emergency or planned CS), enrolment to delivery interval, gestational age, birthweight, Apgar scores, perinatal deaths, Neonatal Intensive Care Unit admission, maternal haemorrhage (antepartum or postpartum) and length of stay.

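### The secondary hypotheses assert no influence on ECV uptake, planned caesarean section and outcomes, but the planned tests of difference can only contradict that, and the trial is not sized for it

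*Protocol article*

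**What the plan says.** The Hypotheses section introduces the secondary hypotheses with "Use of the ECV decision aid by women with a singleton breech-presenting infant in late pregnancy does not influence" and lists three items: uptake of ECV, "the proportion of women having a planned caesarean section for breech presentation at term", and maternal and infant outcomes.

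The Data analysis section gives one rule for all of them: "The secondary outcomes will be compared using chi-square tests of significance for categorical data and t-tests for continuous data". Regression replaces these tests if adjustment is needed. Analyses are by intention to treat.

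The Secondary outcomes section is softer. It says the aid is not meant to steer the decision, and that the investigators will record and "compare the numbers of ECVs undergone and ECV success rate in both arms of the study", along with complications and perinatal outcomes. The Abstract likewise speaks of monitoring service use.

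The Sample size section bases the number of women on two primary outcomes only: decisional conflict, "Assuming a mean difference of -5.75 and standard deviation 13.25, we would need approximately 84 women in each arm", and knowledge, "assuming mean difference of 18.75 and standard deviation of 20, would require only 18 women in each arm". The larger figure is "inflated by 10% to give the effective sample size of 92 women per arm and a total sample of 184 for the trial". No margin, confidence-interval criterion or power is given for the secondary hypotheses.

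**The concern.** A chi-square test or t-test of difference starts from the position that the arms are equal and asks whether the data contradict it. Here that starting position is the hypothesis itself. A significant result would count against the hypothesis. A non-significant result would show only that the data did not contradict it, which in a small trial is likely even when the effect is real.

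The article stresses that the aid was designed to be non-directive. A finding that it left ECV uptake and planned caesarean section unchanged would naturally be cited in support of that. As planned, such a finding could come from imprecision alone. The hypotheses and the tests are both stated in the article and do not match, so this is not a detail left to a fuller document.

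**Working it through.** **1. The stated sample size.** With two-sided significance 0.05 and power 0.8, n per arm = 2(1.960 + 0.842)² × SD² / difference².
- Decisional conflict: 2 × 7.849 × 13.25² / 5.75² = 83.4, so 84. This agrees with the article.
- Knowledge: 2 × 7.849 × 20² / 18.75² = 17.9, so 18. This agrees.
- Inflation: 84 × 1.1 = 92.4, stated as 92.

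The figures reproduce, but neither concerns uptake or mode of delivery.

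**2. Assumed uptake.** The article gives no expected uptake for this trial, so I use a range from its Background.
- Low: 39%, the share of surveyed pregnant women who said they would choose ECV after a brief explanation (22% were unsure).
- High: 69%. In a 1996 study 39 women were offered ECV and 12 decided against it; (39 − 12)/39 = 69%.

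Neither was measured in this trial's population. I use 92 per arm (all randomised) and 84 per arm (the number before the allowance for loss).

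**3. Precision and power.**
- 95% CI half-width = 1.96 × √(2p(1−p)/n). For p = 0.39 and n = 92: 1.96 × √(0.4758/92) = 0.141.
- Power for a rise δ from p₁ to p₂, with mean p̄ = Φ{[δ − 1.96√(2p̄(1−p̄)/n)] / √([p₁(1−p₁) + p₂(1−p₂)]/n)}. For 39% to 49% and n = 92: Φ[(0.1 − 0.1434)/0.0728] = Φ(−0.597) = 0.275.

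| Control uptake | Half-width, n = 92 | Half-width, n = 84 | Power for +10 points, n = 92 | Power for +10 points, n = 84 |
|---|---|---|---|---|
| 39% | 14.1 points | 14.8 points | 0.275 | 0.255 |
| 50% | 14.4 points | 15.1 points | 0.274 | 0.254 |
| 61% | 14.1 points | 14.8 points | 0.298 | 0.276 |
| 69% | 13.4 points | 14.0 points | 0.339 | 0.314 |

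The chance that a true 10-point rise is non-significant runs from 1 − 0.339 = 66% to 1 − 0.254 = 75%. For a 15-point rise, power is 53 to 67% with 92 per arm and 50 to 63% with 84. The smallest rise detectable with 80% power is about 17 to 21 points with 92 per arm and 18 to 22 with 84.

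The half-width depends only on p(1−p), so these figures also apply to planned caesarean section if its rate lies between 31% and 69%. The article gives no expected rate for it.

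**4. What a positive demonstration would need.** Suppose the true difference is zero and the whole 95% CI must lie within ±m. Power = 2Φ(m/SE − 1.96) − 1, floored at zero, with SE = √(2p(1−p)/n). For 80% power, n per arm = 2p(1−p)(1.960 + 1.282)²/m². The margins are illustrations only; ranges are over the uptake rates above.

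| m | Power, n = 92 | Power, n = 84 | n per arm for 80% power |
|---|---|---|---|
| 10 points | 0% | 0% | 450 to 526 |
| 15 points | 6 to 19% | 0 to 11% | 200 to 234 |
| 20 points | 55 to 67% | 47 to 60% | 113 to 132 |

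**5. Rare outcomes.** With no events among 92 women, the exact upper 97.5% bound is 1 − 0.025^(1/92) = 3.9%. Finding no events in either arm would say little about rare perinatal harm.

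**The case against.** The strongest reply is that the over-reading is predicted, not written. The Data analysis section says only that the outcomes will be compared, and gives no rule that a p-value above 0.05 confirms the hypotheses. The Abstract and the Secondary outcomes section describe monitoring and comparison, and Outcomes and significance openly allows that the aid may increase ECV use. Non-directive is defined by intent: a balanced aid could change choices without steering. All of this is fair, and it limits the weight of the point. It does not remove the mismatch, because the Hypotheses section makes no influence a formal hypothesis and the only method named cannot support one.

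Three stronger readings are tempting, and the documents do not support them.
- A reader might infer that the plan declares non-significance to be proof of no influence. It does not say so.
- A reader might infer that a 95% CI could never fit within ±10 points at this size. With 92 per arm that follows only for rates of roughly 14 to 86%; at 10% or 90% the half-width is 1.96 × √(0.18/92) = 8.7 points.
- A reader might infer that comparing ECV success rates breaks intention to treat. The denominator is not stated, success rate is not one of the secondary hypotheses, and the article lacks the inputs needed to size any bias. Only a conditional caution stands: if the rate is taken among women who had ECV, that group is formed after randomisation.

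**Conclusion.** The point holds at moderate severity. The logical mismatch between the secondary hypotheses and their tests rests on no assumed rate. Its practical size does. With control uptake of 39 to 69% and 84 to 92 women per arm, the 95% CI half-width is about 13 to 15 points, and a true 10-point rise would go undetected in about two thirds to three quarters of trials. A non-significant result would therefore leave material influence open.

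It would be wrong to infer that the trial's main conclusions are in doubt. The primary hypotheses, their analyses and the sample size calculated for them are not touched by this point.

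**What to change.** - Reword the secondary hypotheses as estimation of the effect of the aid on ECV uptake and planned caesarean section.
- For both, report the between-arm risk difference with its 95% confidence interval in all randomised women.
- State that a non-significant result will not be read as no influence.
- Allow a conclusion of no influence only if the whole interval lies within a margin that the investigators set and justify before seeing outcome data by arm.
- Label maternal and infant outcomes as descriptive.
- State the denominator of the ECV success rate. If it is women who had ECV, report the rate descriptively. Presentation at birth in all randomised women is not among the database outcomes listed, so I do not assume it is available as a substitute.

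The cost is wording and reporting only: no extra women, and the ECV and mode-of-delivery data are already planned. The downside is a less favourable statement, since the trial will probably have to say that it cannot exclude a moderate effect on uptake.

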#### Interim analysis

An interim analysis will be conducted part way through the study and the results will be reviewed by an independent Data Monitoring Committee. Specifically the incidence of anxiety and decisional conflict in the two randomised groups will be determined after the first 150 women have been enrolled and data have been collected. If there is a significant increase in either of these outcomes at p < 0.01 (1-tailed) with the decision aid, the trial will be stopped. The trial will also be stopped of it is evident that no clear outcome will be obtained.

